### Study aims

The study main aims are: 1) To assess the prevalence of significant liver fibrosis (LSM ≥6.5 kPa) using VCTE, and that of NAFLD (≥225 dB/m) using the CAP in children and adolescents; and 2) To determine the optimal cut-off points of the CAP to achieve maximum concordance with the MRI findings in the diagnosis of mild, moderate and severe liver steatosis in children and adolescents.

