### Sample size calculation

The school population aged between 9 and 16 in Mataró stands at 11,503 individuals [45]. These are approximately equally distributed between the 4 groups: male/female between 9 to 12 and 13 to 16 years old.

We expect that 8% of this population will have NAFLD and 2% will have liver fibrosis. A sample size of 2,866 students will allow us to estimate a prevalence of NAFLD stratified by age (9–12, 13–16 years) and sex of 8%, with a precision of 2% in each stratum, and a prevalence of fibrosis of 2%, with a precision of 1% in each stratum. We anticipate that blood samples will be available in 50% of the sample and MRI in 70%. MRI will be offered to all LSM/CAP positive subjects (LSM ≥6.5 kPa / CAP ≥225 dB/m) and, randomly, to 10% of those with negative LSM/CAP (LSM <6.5 kPa / CAP <225 dB/m). This will add up to 1,433 blood tests and 424 MRIs.

With the proposed sample we can find a concordance of 80% with a precision of 4% using kappa indices, or an intraclass correlation coefficient of 0,8 with a precision of 2,5% (8% and 4% precision for kappa and ICC, respectively, using only 424 MRIs). This sample size has been calculated assuming a design effect of 20%, an alpha error of 5%, a power of 80% and bilateral contrasts.

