### Statistical analyses

Prevalences of NAFLD and fibrosis will be calculated using CAP ≥225dB/m and LSM ≥6.5kPa, respectively. They will be calculated by sex and age (9–12 and 13–16 years) and 95% confidence intervals will be provided.To determine the optimal CAP cut-off point that best fits the 4 MRI categories, the relationship between CAP and MRI will be explored graphically, CAP means for each MRI category will be compared by ANOVA, 2-to-2 ROC curves will be used, and a multi-class ROC curve will be used to obtain the overall area under the curve for the finally chosen points. In addition, dichotomous CAP classifications (normal/altered) will be compared with MRI levels using contingency tables and chi-square tests.To identify the variables related to NAFLD, multivariate models will be used using NAFLD as the dependent variable and possible risk and confounding factors as independent variables.Concordance between the diagnosis of NAFLD or fibrosis obtained by different methods (CAP vs FLI, LSM vs PNFI, LSM vs PNFS) will be assessed by kappa indices (when using the dichotomised version of these variables) and by the intraclass correlation coefficient (when using the continuous version of the variables). The best cut-off point in PNFI and PNFS will be chosen to detect fibrosis using LSM ≥6.5 kPa as the standard test in the diagnosis of fibrosis using ROC curves.The construction of the biomarker to detect the presence of steatosis in children and adolescents will be carried out using the coefficients of multivariate logistic regression models, where steatosis (CAP >225 dB/m) will be the dependent variable and the rest of the variables will be potential explanatory variables that may form part of the marker.

To take into account that participants come from selected schools, hierarchical models will be used when necessary. All tests will be bilateral, with a significance of 5%. We do not plan to use missing data imputation methods as we expect very few missings beyond those already considered. Stata17 statistical package will be used.

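### The precision quoted for the 424 MRIs is for kappa and ICC, but the CAP–MRI analysis uses neither, and no agreement coefficient is named for the graded cut-offs of Aim 2

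*Protocol article*

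**What the plan says.** Aim 2 (Study aims) is to find the "optimal cut-off points of the CAP to achieve maximum concordance with the MRI findings" for mild, moderate and severe steatosis. The matching main outcomes are the accuracy of CAP against MRI and the cut-offs themselves.

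The Sample size calculation expects MRI in all VCTE-positive children, subject to 70% availability, and "randomly, to 10% of those with negative LSM/CAP", giving 424 MRIs. It assumes a concordance of 80% and an ICC of 0.8, with a design effect of 20%. For the MRI subset it states "8% and 4% precision for kappa and ICC, respectively, using only 424 MRIs", and no precision of any other kind.

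For CAP against MRI, the Statistical analyses section says "CAP means for each MRI category will be compared by ANOVA, 2-to-2 ROC curves will be used". It adds a graphical exploration, a multi-class ROC curve with an overall AUC at the chosen points, and contingency tables with chi-square tests of normal/altered CAP against MRI level. Agreement coefficients come later in the same section, where concordance between "different methods (CAP vs FLI, LSM vs PNFI, LSM vs PNFS) will be assessed by kappa indices", or by ICC for the continuous versions.

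**The concern.** The two sections do not fit together. One quotes precision for kappa and ICC on the MRI subset. The other assigns kappa and ICC to a list of pairs from which MRI is absent, and gives the CAP–MRI comparison other statistics whose precision is not stated.

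The planned statistics also answer different questions from the one in Aim 2. ANOVA and chi-square test whether CAP and MRI are associated at all, and both can be highly significant when grades often disagree. AUC measures how well CAP ranks children. None says how often a CAP grade matches the MRI grade once the cut-offs are fixed. A reader could also take ±8% or ±4% as the precision of the CAP–MRI result.

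**Working it through.** **Inputs (Sample size calculation):** 2,866 children; 8% NAFLD; MRI availability 70%; 10% of VCTE-normals; kappa 0.80; ICC 0.8; design effect 1.2. Effective n for 424 MRIs = 424/1.2 = 353.3.

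**1. Where 424 comes from.** 0.70 × 0.08 × 2,866 = 160 positives; 0.10 × 0.92 × 2,866 = 264 normals; total 424. This is the offer rule plus uptake. No concordance formula is involved.

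**2. The stated ICC precision.** 1.96 × (1 − 0.8²)/√(353.3 − 1) = 1.96 × 0.36/18.77 = 0.038. This reproduces the stated 4%. As arithmetic it is sound, but CAP is in dB/m and MRI gives a fat percentage, so an ICC between them is not interpretable.

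**3. The stated kappa precision.** Large-sample (Fleiss–Cohen–Everitt) standard error for a 2×2 table with equal margins, kappa 0.80, effective n 353.3; half-width 1.96 × SE:

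| Margin (both methods) | Half-width |
|---|---|
| 8% | ±11.8 points |
| 20% | ±7.9 points |
| 40% | ±6.4 points |

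The stated 8% is matched at about 20%, a margin the article does not give.

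The scanned set is also not a simple sample: 160/424 = 38% are CAP-positive, if all VCTE-positives are counted as such. Assume 8% positive by both methods and kappa 0.80 in the population. Each discordant cell is 0.2 × 0.08 × 0.92 = 0.0147, so PPV = (0.08 − 0.0147)/0.08 = 0.816 and the MRI-positive rate among VCTE-normals is 0.0147/0.92 = 1.6%. Simulating 160 positives and 264 normals at these rates, with design effect 1.2, gives:
- kappa in the enriched set, unweighted: about 0.83 ± 6 points;
- kappa weighted to the population: 0.80 ± 9.5 points.

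The precision thus depends on margins and weighting, neither of which is stated.

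**4. Precision of what is planned: AUC.** Hanley–McNeil SE × √1.2, AUC 0.80, 424 scans. The number of MRI-positive children is not given, so it is varied: 10 gives ±0.18; 20, ±0.13; 50, ±0.083; 160, ±0.050; 200, ±0.047. For a pairwise curve between small categories, 10 against 30 gives ±0.195 and 30 against 100 gives ±0.111.

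**5. Precision of what is planned: sensitivity at 225 dB/m.** With f the MRI-positive rate among VCTE-normals, S = 0.08·PPV/(0.08·PPV + 0.92·f), and the half-width is about 1.96·S(1 − S)·√[(1 − PPV)/(160·PPV) + (1 − f)/(264·f)]. At f = 1.6%, S = 0.816 and the half-width is 1.96 × 0.150 × √(0.0014 + 0.2330) = 0.14. Almost all of it comes from 264 × 0.016 = 4.2 expected MRI-positive normals. Holding PPV at 0.816 and simulating, before design effect:

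| f (assumed) | Sensitivity (simulated mean) | Half-width |
|---|---|---|
| 0.5% | 94% | ±10 |
| 1.6% | 82% | ±14 |
| 3% | 71% | ±14.5 |
| 5% | 59% | ±13 |

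The design effect multiplies these half-widths by √1.2 = 1.10.

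**The case against.** The best defence is that the plan is sensible and the wording merely incomplete. ROC analysis is a standard way to choose cut-offs, and it fits the main outcomes, which speak of accuracy. The contingency tables show directly how normal/altered CAP agrees with MRI. The sample-size text mentions kappa on the MRIs, so a CAP–MRI kappa may have been intended and may appear in a fuller plan.

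Much of this stands, and it rules out three stronger readings that a reader might infer:
- *That the MRI sample was calculated from the wrong formula.* Step 1 shows it follows from the offer rule and uptake; kappa and ICC are only the precision reported at that number.
- *That agreement with MRI is left wholly unexamined, or that ROC is the wrong tool.* The contingency tables and AUC do describe the relation. What is missing is a named agreement measure for the graded cut-offs. Nor does the article present chi-square as proof of agreement.
- *That ±14 points for sensitivity shows the stated ±8% to be false.* These are different quantities; the article claims nothing about sensitivity, and ±14 needs equal margins and f = 1.6%, neither of which it gives.

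The defence does not remove the mismatch. It is not simply detail left to a fuller document: both statements are in the article, and the list of pairs given kappa and ICC leaves MRI out.

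**Conclusion.** The point holds as an inconsistency between two sections that bears on a main aim. The precision quoted for the MRI subset attaches to no analysis planned for it, and the concordance in Aim 2 has no coefficient for graded steatosis.

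Its size is moderate. The 424 and the ICC arithmetic reproduce. The kappa ±8% reproduces only under an inferred 20% margin; at the plan's 8%, a binary kappa of 0.80 carries about ±9.5 to ±12 points. No single figure covers the AUC or sensitivity results, whose ranges rest on assumed MRI category counts and assumed MRI-positive rates among VCTE-normals. The weighted figures also assume that uptake of MRI is unrelated to its result. The choice of cut-offs by ROC is not in question.

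**What to change.** **Statistical analyses.** Add a weighted kappa with 95% CI between the CAP classes at the chosen cut-offs and the four MRI classes, weighted back for the 10% sampling of VCTE-normal children. Keep the ROC analysis for choosing the cut-offs. State that the chi-square tests are not read as evidence of agreement.

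**Sample size calculation.** Drop the ICC ±4% for CAP against MRI. Recompute the kappa precision for the analysis actually planned, with its margins and weighting stated. Do not carry ±8% over, since it matches only a binary, unweighted kappa and not a four-class weighted one. Add the precision of AUC or sensitivity as a range under stated assumptions, for example roughly ±10 to ±15 points for population sensitivity at 225 dB/m if 0.5% to 5% of VCTE-normals are MRI-positive, before design effect. A single ±14 should not be presented as derived from the plan.

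**Cost.** One extra statistic on data already being collected, and a less favourable precision statement. No further MRIs and no change to study procedures.

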### Statistical analyses

Prevalences of NAFLD and fibrosis will be calculated using CAP ≥225dB/m and LSM ≥6.5kPa, respectively. They will be calculated by sex and age (9–12 and 13–16 years) and 95% confidence intervals will be provided.To determine the optimal CAP cut-off point that best fits the 4 MRI categories, the relationship between CAP and MRI will be explored graphically, CAP means for each MRI category will be compared by ANOVA, 2-to-2 ROC curves will be used, and a multi-class ROC curve will be used to obtain the overall area under the curve for the finally chosen points. In addition, dichotomous CAP classifications (normal/altered) will be compared with MRI levels using contingency tables and chi-square tests.To identify the variables related to NAFLD, multivariate models will be used using NAFLD as the dependent variable and possible risk and confounding factors as independent variables.Concordance between the diagnosis of NAFLD or fibrosis obtained by different methods (CAP vs FLI, LSM vs PNFI, LSM vs PNFS) will be assessed by kappa indices (when using the dichotomised version of these variables) and by the intraclass correlation coefficient (when using the continuous version of the variables). The best cut-off point in PNFI and PNFS will be chosen to detect fibrosis using LSM ≥6.5 kPa as the standard test in the diagnosis of fibrosis using ROC curves.The construction of the biomarker to detect the presence of steatosis in children and adolescents will be carried out using the coefficients of multivariate logistic regression models, where steatosis (CAP >225 dB/m) will be the dependent variable and the rest of the variables will be potential explanatory variables that may form part of the marker.

To take into account that participants come from selected schools, hierarchical models will be used when necessary. All tests will be bilateral, with a significance of 5%. We do not plan to use missing data imputation methods as we expect very few missings beyond those already considered. Stata17 statistical package will be used.

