Diagnosis of NAFLD should be considered in paediatric population with excess weight, especially in those >10 years of age, with arterial hypertension (AHT), DM, IR or metabolic syndrome (MetS). In clinical practice, screening begins with anamnesis, physical examination, blood test and abdominal ultrasound, which help to establish a differential diagnosis with other entities. However, liver biopsy remains the gold standard for assessing disease progression, although its use is limited by its invasiveness and potential complications [8]. Some authors consider screening with transaminases, but these may still be normal in patients with NAFLD [5]. In terms of imaging, abdominal ultrasound, which is an affordable and safe technique, is only able to detect fatty infiltration above 30% [9]. Magnetic resonance imaging (MRI) is more accurate in diagnosing NAFLD, showing high sensitivity and specificity [10]. Nevertheless, its high cost and limited availability make it an invalid method for population screening.

Therefore, non-invasive serological and elastographic diagnostic methods are being developed. The most widely used is Vibration-Controlled Transient Elastography (VCTE), which non-invasively determines the presence of fibrosis by measuring liver stiffness (LSM) with the FibroScanⓇ (FS) device [11]. Multiple studies have demonstrated its usefulness in adults [11, 12], so it may also be appropriate for children and adolescents [5, 11]. Normal LSM values may vary according to age, ranging from 3.4–5.1 kPa [13, 14, 16]. Above this threshold, values correlate with different stages of fibrosis on the METAVIR scale: 5–7 kPa is indicative of F1; 7–9 kPa, F1-F2; and >9 kPa, F3-F4 [15, 16]. FibroScan features the Controlled Attenuation Parameter (CAP), which allows quantification of hepatic fat >11%. CAP values correlate with the degree of steatosis and a cut-off point of ≥225 dB/m is used for its detection [17, 18]. Furthermore, serological markers are used for diagnostic approaches to NAFLD and fibrosis. In adults, the Fatty Liver Index (FLI) [19] (NAFLD) as well as the NAFLD Fibrosis Score and FIB-4 (fibrosis) are commonly used [20] but these do not provide accurate results in the paediatric population [8, 21]. Thus, specific markers have been developed for these patients, such as the Pediatric NAFLD Fibrosis Index (PNFI) [22] and the Pediatric NAFLD Fibrosis Score (PNFS) [23], with an AUROC of 0.85 and 0.74 respectively [22, 23].

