### Main outcome measures

Percentage of subjects with LSM ≥6.5 kPa by VCTE in the general population aged ≥9 to ≤16 years.Percentage of subjects with CAP ≥225 dB/m by VCTE in the general population aged ≥9 to ≤16 years.Comparison of liver steatosis diagnosis accuracy between CAP by VCTE and MRI in the general population aged ≥9 to ≤16 years.Determination of optimal cut-off points of the CAP for the diagnosis of mild, moderate and severe liver steatosis in children and adolescents.

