LSM is performed in all patients using VCTE with the Fibroscan® (FS) system (Echosens, France). LSM is performed with S, M or XL probe following the Automatic Probe Selection tool available on the FS. The FS used is the 430 MINI. FS measures the hepatic elasticity of a cylinder approximately 1 cm in diameter by 4 cm in length [41]. FS transmits, via a probe, a vibration that propagates through the liver. The speed of propagation of the vibration correlates with the stiffness (in kPa) of the liver tissue and allows estimation of the fibrosis degree. In order for VCTE to be valid, 10 correct determinations with an interquartile range (IQR) <30 and a success rate >60% must be obtained. Significant liver fibrosis by VCTE is being defined by a LSM ≥6.5 kPa [13–16].Fibrosis scores/serum biomarkers: Pediatric NAFLD Fibrosis Index (PNFI) and Pediatric NAFLD Fibrosis Score (PNFS) are being used to estimate fibrosis degree. Significant liver fibrosis is being defined when the values of the different scores are above the following cut-offs, according to literature: PNFI ≥9, PNFS ≥13 [22, 23, 42, 43].

**Liver steatosis** is estimated using three methods: CAP, liver steatosis score and MRI.

CAP using VCTE is used to measure liver steatosis with the FS using either S, M or XL probe at the time of LSM. Liver steatosis is diagnosed when the value of CAP ≥225 dB/m [13–16].Liver steatosis is measured by the steatosis score Fatty Liver Index (FLI) which is based on: WC, BMI, TG and GGT [19]. Significant liver steatosis is defined when FLI ≥60 according to literature [44].Liver steatosis measured by MRI. It is performed using the Magneton Essenza 1.5 Tesla Aera system (SIEMENS), with the integration of Tim technology and Dot Engines (Day Optimizing through put Engines) application packages. The result obtained is the steatosis score or steatosis degree corresponding to the percentage of hepatocytes containing fatty vacuoles with respect to the hepatic fat fraction. Thus, a differentiation is made among mild steatosis (5–29% of hepatocytes affected), moderate steatosis (30–59% affected) and severe steatosis (more than 60% of hepatocytes affected). MRI is performed on all participants with altered VCTE results (≥6.5 kPa and/or ≥225 CAP) and 10% of participants with normal VCTE results (<6.5 kPa or <225 CAP).

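### The raw share with CAP ≥225 dB/m is reported as NAFLD prevalence, and the planned MRI results are not used to show how far CAP error moves it

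*Protocol article*

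**What the plan says.** - **Estimator.** Under Statistical analyses, "Prevalences of NAFLD and fibrosis will be calculated using CAP ≥225dB/m and LSM ≥6.5kPa, respectively", by sex and age group with 95% confidence intervals. The matching main outcome is "Percentage of subjects with CAP ≥225 dB/m by VCTE in the general population".
- **Second main aim.** "To determine the optimal cut-off points of the CAP to achieve maximum concordance with the MRI findings". The analysis for it is meant "To determine the optimal CAP cut-off point that best fits the 4 MRI categories", so the boundary between no steatosis and mild steatosis is included.
- **Use of MRI.** Besides plots, ANOVA and ROC curves, "dichotomous CAP classifications (normal/altered) will be compared with MRI levels using contingency tables and chi-square tests". Nothing carries these results into the prevalence.
- **MRI sampling.** The Sample size calculation offers MRI to every LSM- or CAP-positive child and to a random 10% of the negatives, with 70% availability and 424 scans expected.
- **Planning value.** "We expect that 8% of this population will have NAFLD", with a precision of 2 points in each of four age-sex strata.
- **Thresholds.** The Introduction describes CAP as a measure "which allows quantification of hepatic fat >11" percent. Under Data collection and measuring tools, MRI grading starts at "mild steatosis (5–29% of hepatocytes affected").

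**The concern.** Aim 1 treats a positive CAP as NAFLD, while Aim 2 treats the relation of CAP to steatosis in children as still to be established. The same report could then give a NAFLD prevalence at 225 dB/m and, a few paragraphs later, a different best cut-off for any steatosis.

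The document's own fat thresholds (above 11% for CAP, from 5% for MRI) also suggest that the two definitions do not coincide.

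At a prevalence near 8%, a modest loss of specificity acts on the 92% of children without steatosis and can raise the positive share by several points. A larger sample narrows the interval around the CAP-positive share but does not remove that shift. The design already contains a two-phase sample that could show its size, and the planned prevalence analysis leaves it unused.

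**Working it through.** **1. The plan's own figures reproduce.** Per stratum, n0 = 1.96²·p(1−p)/d². Then apply the finite population correction with 11,503/4 ≈ 2,876 children, multiply by the design effect 1.2, and multiply by 4 strata.
- Fibrosis (p = 2%, d = 1 point): n0 = 752.9; corrected 596.7; × 1.2 × 4 = 2,864, against 2,866 stated.
- NAFLD (p = 8%, d = 2 points): the same steps give 2,723. With 2,866 children the half-width is about ±1.94 points per stratum.
- MRI: 8% of 2,866 is 229 positives, leaving 2,637 negatives. 0.7 × 229 + 0.1 × 2,637 = 160 + 264 = 424, as stated.

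**2. What the raw share estimates.** Raw share q = 0.08·Se + 0.92·(1 − Sp). Se and Sp are assumptions. PPV = 0.08·Se/q.

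| Se / Sp | True positives | False positives | Raw share | Shift from 8% | PPV |
|---|---|---|---|---|---|
| 60% / 97% | 4.8% | 2.8% | 7.6% | −0.4 | 63% |
| 70% / 95% | 5.6% | 4.6% | 10.2% | +2.2 | 55% |
| 80% / 90% | 6.4% | 9.2% | 15.6% | +7.6 | 41% |
| 90% / 85% | 7.2% | 13.8% | 21.0% | +13.0 | 34% |

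With Se = 80%, the raw share equals the truth only at Sp = 1 − 0.016/0.92 = 98.3%. Three of the four scenarios shift the estimate by more than the planned ±2 points.

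**3. What the MRI sample can deliver.** Two-phase estimate: π = q·PPV + (1 − q)·f, where f is the steatosis rate on MRI among children with normal results.

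Variance ≈ q²·PPV(1 − PPV)/n1 + (1 − q)²·f(1 − f)/n0 + (PPV − f)²·q(1 − q)/2,866, where n1 and n0 are now the numbers scanned. With 70% uptake in both groups, n1 = 0.7·2,866·q and n0 = 0.7·0.1·2,866·(1 − q). For simplicity the two groups are defined by CAP alone, and clustering is left out.

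Example at 80/90: q = 0.156, PPV = 0.410, f = 0.016/0.844 = 0.0190, n1 = 313, n0 = 169. The three terms are 0.0000188 + 0.0000782 + 0.0000070 = 0.000104, so SE = 0.0102 and the half-width is ±2.0 points. About three quarters of the variance comes from the scanned normals.

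| Se / Sp | n1 | n0 | Expected steatosis among scanned normals | Half-width overall | Per stratum (×2) |
|---|---|---|---|---|---|
| 60 / 97 | 152 | 185 | 6.4 | ±2.6 | ±5.1 |
| 70 / 95 | 205 | 180 | 4.8 | ±2.3 | ±4.6 |
| 80 / 90 | 313 | 169 | 3.2 | ±2.0 | ±4.0 |
| 90 / 85 | 421 | 158 | 1.6 | ±1.6 | ±3.3 |

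A second calculation uses the planned 160 and 264 scans, q = 8%, PPV 0.3 to 0.9, f 0.5% to 4%, and a design effect of 1.2 on q. It gives about ±1.0 to ±2.4 overall and ±2.0 to ±4.8 per stratum.

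**4. Who counts as normal.** Study design describes the 10% group as CAP below 225 and/or LSM below 6.5. Data collection and measuring tools uses *or*. Read literally, a child with CAP ≥225 and LSM <6.5 falls in both the altered and the normal group, so the sampling weights are not defined until this is settled.

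**The case against.** The case on the other side is substantial.

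- **The outcome is openly defined.** Main outcome measures states it as a share above a CAP threshold, and the cut-off is taken from cited literature. Fixing it in advance also avoids choosing a cut-off on the same data. This stands, and it is why the CAP share should be kept. What remains is that the aims, the analysis section and the expected results call it NAFLD prevalence.
- **Is 225 dB/m to be replaced?** A reader might infer this from Aim 2. The document speaks only of determining optimal cut-offs and nowhere says that 225 is abandoned. What it does support is that the lowest boundary is derived again.
- **Do false positives dominate the count?** They outnumber true positives in only two of the four assumed scenarios, and at 60/97 the error is 0.4 points. Since no accuracy figures are given, a large bias is possible but not shown.
- **Is the result tested against 8%?** No. The 8% is a planning value and a stated expectation; no comparison with it is planned.
- **Should the MRI figure become the NAFLD prevalence, at no cost?** No. It needs no further scans, but by stratum it misses the planned ±2 points. With 1.6 to 6.4 expected cases among all scanned normals, stratum estimates and a school bootstrap within strata would be unstable. MRI steatosis alone also does not meet the Introduction's definition of NAFLD, which excludes toxic alcohol use and other liver disease.
- **The article is condensed.** A supplementary estimator could sit in an analysis plan that is not shown, and the planned CAP-by-MRI tables would expose some misclassification. That softens the point. However, the prevalence estimator is stated in the article, and pooled tables do not give a population figure without weighting for the scan fractions.

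**Conclusion.** The point holds as a cheap improvement. The plan reports a CAP-positive share as NAFLD prevalence while gathering, but not using, the data that would show how far the two differ. Over the assumed range the raw share is 7.6% to 21.0% for a true 8%, so the bias runs from negligible to well beyond the planned ±2 points.

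This rests on assumed sensitivity and specificity and on a true prevalence equal to the planning value. The 11% and 5% thresholds show that the definitions differ as described. One refers to hepatic fat and the other to affected hepatocytes, so they cannot be turned into a sensitivity. The documents do not support the stronger conclusions that the headline figure will be badly wrong or that it should be withdrawn. The point concerns steatosis only, because no MRI reference for fibrosis is planned.

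**What to change.** 1. Keep the pre-specified share with CAP ≥225 dB/m, overall and by age-sex stratum, and label it *elevated CAP (CAP-defined steatosis)*.
2. Add one overall, co-reported MRI-based steatosis prevalence. Weight each MRI result by the inverse of the fraction actually scanned within two groups that follow the VCTE selection rule: CAP ≥225 and/or LSM ≥6.5, versus both below.
3. Use a confidence interval that allows for school clustering and for few events among the scanned normals.
4. First reconcile the *and/or* wording for normals in Study design with the *or* wording in Data collection and measuring tools.
5. State the assumption that scanned children resemble those not scanned, including the substitutes offered a scan when another child does not tolerate it (Risks and disadvantages for patients).

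**Cost.** No additional scans: one more estimator, a label and clearer selection wording. The downside is lower precision: about ±1.6 to ±2.6 points overall at 70% uptake before clustering, and about ±3.3 to ±5.1 per stratum. The MRI-based figure should therefore not be reported by stratum.
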